**However, this study had certain limitations that affects the generalisability of the findings:**

1. Use of 4 different NIRS devices with an adult sensor: There are systematic differences in the measurement with different devices and different sensors (adult versus neonatal sensors) (15, 16). Studies using adult sensors have reported 55%-85% as the normal range for cerebral tissue oxygenation (17). When using newborn sensors, the lower range of normal has been reported as 65% (mean difference of 10%). Where an adult sensor is used, a correction factor needs to be applied to generate measurements equivalent to newborn sensors. In our study, we chose the range of 65% - 90% based on review of literature and local data from monitoring of preterm infants at Westmead Hospital's NICU.
2. Changing the intrinsic alarm mechanism: use of a "burden alarm" that warned when hypoxia or hyperoxia was accumulating. This is in contrast to real world situation where the device alarms within 1.5 seconds of deviation from the target range.
3. Use of an aggressive dedicated clinical treatment guideline in SafeBoosC II study. For example, as per SafeBoosC II study: 'if the cerebral oxygenation is below 55%, then assess cardiovascular status. If Blood pressure below the normal range or low, even in the normal range, consider Vasopressor-inotropes, Fluid bolus (normal saline), Decrease mean airway pressure'.

In summary, SafeBoosC II study found a significant reduction in the burden of cerebral hypoxia and hyperoxia in the group that were randomised to cerebral oxygenation monitoring combined with a dedicated clinical treatment guideline (experimental group) versus the group with blinded NIRS monitoring and treatment as usual (control group). Could this finding be explained by aggressive clinical approach in experimental group, and /or heterogeneity in the equipment used, this remains unknown. It is also important to note that NIRS offers a role in monitoring regional tissue oxygenation.

In our study, we are addressing weaknesses from SafeBoosC II study by:

- (i) eliminating equipment heterogeneity (by using same NIRS equipment and non-adhesive neonatal NIRS sensor),
- (ii) by using non-adhesive sensors, the risk of skin injury is extremely low and
- (iii) less aggressive clinical guideline to ensure harm from unnecessary treatment is reduced and
- (iv) inclusion of long-term neuro-developmental follow up.

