#### Exclusion criteria:

- Infants admitted to NICU beyond 6 hours of age.
- Infants with an antenatal or postnatal diagnosis of major congenital anomaly requiring major surgery or a genetic disorder associated with neurological impairment.
- Multiple births beyond twins are excluded for practical reasons (sites may not have additional NIRS monitors and the rates of multiple births beyond twins in Australia and New Zealand is very low < 2%).

3. This trial will be a multi-site, international study. Participating sites will be NICUs skilled with provision of tertiary level of intensive care services to preterm infants born < 29 weeks gestation.

4. The study design will assist in assessment of the primary outcome that is ‘in premature babies (< 29 weeks gestation at birth), can dedicated treatment using cerebral oximetry compared to usual treatment, reduce the burden of cerebral hypoxia and hyperoxia in the first 5 days”? A RCT will detect any difference in hypoxia and hyperoxia burden between groups (primary outcome) and allow exploration of secondary outcomes.

5. The following data will be collected:

A. Cerebral oxygenation and physiological data:

- NIRS device collects data in real time at 1.5 seconds interval. This data is stored in the memory drive of the SenSmart device. Data from each patient will be downloaded using a SenSmart data management software (this software is available at each site for the study) after the completion of the monitoring period (5 days). This data will be stored in CSV format. This data will be read by local PI and then by the central reporting team at Westmead Hospital. Data will be transferred using secure work-based email or Accellion App or secure transfer platforms as approved by the local health authorities. File will be coded by the local PI; central reporting team will have de-identified version of the file.

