#### 6.5 STUDY METHODOLOGY

Enrolment will occur after birth of the baby. After enrolment, infants will be randomised to either control group or intervention group. For all enrolled babies, monitoring of cerebral oxygenation will be commenced by placement of a non-adhesive probe on the fronto-parietal region of the forehead within 6 hours of birth and monitoring will be continued for 5 days.

For the Intervention group:

For the intervention group, the cerebral oxygenation reading is visible and the baby will be treated according to a dedicated clinical guideline when the cerebral oxygenation is outside the range of 65%-90% as shown in Figure 1 and Figure 2. The sensor site will be inspected based on the unit's practice of skin assessment to ensure correct sensor placement and skin integrity.

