### Outcomes

| Tool                 | Outcomes                                                                                                                                            | Time points                                                                   |
|-----------------------------|------------------------------------------------------------------------------------------------------------------------------------------------------------|--------------------------------------------------------------------------------------|
| Cerebral NIRS monitors      | Burden of hypoxia and hyperoxia expressed as percentage time spent < 65% and > 90%.                                                                        | First 5 days of monitoring period                                                    |
| Medical records             | Mortality rates                                                                                                                                            | Prior to home discharge                                                              |
| Cerebral imaging            | Evidence of brain injury on cranial ultrasounds and MRI brain (when performed for clinical reasons)                                                        | Prior to home discharge                                                              |
| Medical records             | Presence of neonatal morbidities (chronic lung disease, necrotizing enterocolitis, retinopathy of prematurity)                                             | Prior to home discharge                                                              |
| Neuro-developmental testing | 

General movement assessment

Cognition, motor and language domain scores on Bayley Scales of Infant

 | At 4 months (CGA)

At 12 months (CGA), 18-24 months (CGA), and 5 years of age. |

|                                 |                                                                                                                                  |                                   |
|---------------------------------|----------------------------------------------------------------------------------------------------------------------------------|-----------------------------------|

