### *Analysis of the outcomes*

Participant demographic and clinical characteristics and study outcomes will be presented using standard descriptive statistics: frequencies and percentages for categorical variables, mean, standard deviation and range or median, quartiles and range for continuous variables. All efficacy analyses will be performed according to randomized treatment. We will use a suitable transformation to ensure normality for the primary outcome, the burden of cerebral hypoxia and hyperoxia and use generalized estimating equation (GEE) or a similar method for comparison between groups. Sub-group analysis for stratification variables will be performed. For reporting the burden of cerebral hypoxia and hyperoxia, we will include deviations in cerebral oxygenation more than a minute. This pragmatic approach will ensure we achieve a balance between responding to an alarm from poor sensor contact with the participant and identifying true real-time changes in cerebral oxygenation. To allow comparison of the primary outcomes with other studies, we will also report the burden of cerebral hypoxia and hyperoxia more than 10 minutes. Other study outcomes will be compared using similar methods, using GEE methods with normal or binary outcome distribution and correlation between outcomes in twins. Adjusted models will explore predictors out outcomes. No corrections for multiple hypotheses will be performed. Adjusted models will be used to explore predictors of outcomes. Variables that differed significantly between the two groups, and could plausibly contributory to the outcome, will be considered for adjustment. A fixed adjustment for gestational age category will be included as an a priori specified variable. For this trial, no imputation of missing data will be performed and sensitivity analysis will only be performed separately for the burden of cerebral hypoxia and cerebral hyperoxia. In future, sensitivity analysis may be performed for variables such as specific gestational age or treatment received.

Withdrawn participants will be replaced in the study with new randomisation (per protocol). To facilitate and ensure long term follow up, existing measures which are standard practices includes providing appointment letters by post, reminding and confirming with families by phone and/or text message when follow up appointment is close to date.

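### The SAP counts only deviations longer than one minute, the protocol's burden has no minimum length, and no unfiltered analysis is planned, so the reported effect can differ from the effect on total time out of range

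*Combined protocol and SAP*

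**What the plan says.** **Outcome definition.** Protocol section 5.4 and the SAP's Primary outcome statement give the burden over the first 5 days in percent hours. The Outcomes table in protocol section 6.5 has "Burden of hypoxia and hyperoxia expressed as percentage time spent < 65% and > 90" (per cent). None of the three sets a minimum duration.

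**Analysis.** The SAP, Analysis of the outcomes, states: "For reporting the burden of cerebral hypoxia and hyperoxia, we will include deviations in cerebral oxygenation more than a minute". The reason given is to "achieve a balance between responding to an alarm from poor sensor contact with the participant and identifying true real-time changes in cerebral oxygenation". For comparison with other studies, "we will also report the burden of cerebral hypoxia and hyperoxia more than 10 minutes". On robustness, "sensitivity analysis will only be performed separately for the burden of cerebral hypoxia and cerebral hyperoxia".

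**Data.** Protocol section 6.2, item 5A: "NIRS device collects data in real time at 1.5 seconds interval". The SAP's data-cleaning paragraph removes readings of 0 and 100 and keeps other artifacts. Neither document says when a run ends, whether a removed or missing sample breaks it, or whether a qualifying run counts in full.

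**Difference between arms.** In the intervention arm, "the baby will be treated according to a dedicated clinical guideline when the cerebral oxygenation is outside the range of 65%-90" (per cent; section 6.5). In controls the screen is covered and the range alarms are off, while sensor-contact alarms stay on (section 6.4 and the SAP's blinding section). Section 4.3 says that in ordinary use "the device alarms within 1.5 seconds of deviation from the target range".

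**The concern.** The filter acts on episode length. That is measured after randomisation, and the intervention may alter it: staff in one arm see the reading and hear range alarms, and Figures 1 and 2 move to clinical checks only after sensor repositioning has made no difference. An episode brought below the cut-off contributes nothing to the filtered burden, although some time out of range remains. An episode broken into two runs loses any piece at or below the cut-off, even if total time is unchanged. With a sample every 1.5 seconds (40 per minute) and no run-end rule, a single in-range or removed sample might restart the clock.

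At stake is the headline estimate. The hypothesis is a halving of burden, so a few points around 50% affect how the result is read. The ten-minute figure, meant for comparison with other trials, is the more sensitive of the two.

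**Working it through.** **The plan's own figures.** log10(0.5) = -0.301, which matches the stated 0.3. Normal approximation: 2 × (1.96 + 0.8416)² × 0.5² / 0.3² = 43.6 per group; the t-based version gives 44.6, rounded up to 45. Design effect 1 + 0.3 × 0.1 = 1.03, and 45 × 1.03 = 46.35, so 47 per group and 94 in total. The sample size reproduces and does not depend on the filter.

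**Assumptions for the check.** The documents give no episode lengths. I take exponential lengths with mean m minutes in controls, a cut-off of c minutes, and a qualifying run counted in full. Burden is measured as time out of range, as in the Outcomes table.

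**Formulas.**
- Time retained per episode: f(m, c) = (m + c) × exp(-c/m).
- Every episode halved (true reduction 50%): shown reduction = 1 - f(m/2, c) / f(m, c).
- Every episode split once at a uniformly random point (true reduction 0%): shown reduction = (c²/m) × E1(c/m) / f(m, c), where E1 is the exponential integral.

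Example, m = 3 and c = 1: f(3, 1) = 4 × exp(-1/3) = 2.866 and f(1.5, 1) = 2.5 × exp(-2/3) = 1.283, so the shown reduction is 1 - 1.283/2.866 = 55.2%.

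| Mean length (min) | Halved, >1 min | Split, >1 min | Halved, >10 min | Split, >10 min |
|---|---|---|---|---|
| 20 | 50.2% | 0.6% | 60% | 15% |
| 10 | 50.6% | 1.8% | 72% | 30% |
| 5 | 52.2% | 5.0% | 89% | 48% |
| 3 | 55.2% | 9.6% | 97% | 62% |
| 1 | 72.4% | 30% | - | - |

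Each row is one population, so both cut-offs can be read for the same infants. With lognormal lengths (median 1 or 3 minutes, log-SD 1.0 or 1.5), a true 50% reads as 51-63% under the one-minute rule.

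**Direction.** If treatment multiplies every length by k < 1, the filtered ratio is k × E[D; D > c/k] / E[D; D > c]. This is never above k, so proportional shortening cannot understate the reduction. Two other mechanisms behave differently:
- Half as many episodes, lengths unchanged: both measures show 50%, so there is no bias.
- Half of the episodes of 2 minutes or less removed, m = 1: the true reduction is 0.5 × (1 - 3 × exp(-2)) = 29.7%. The one-minute measure shows 0.5 × (2 × exp(-1) - 3 × exp(-2)) / (2 × exp(-1)) = 22.4%. The filter understates the benefit.

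**Effect on the test.** With 47 per group, SD 0.5 and design effect 1.03, the standard error is 0.5 × √(2 × 1.03/47) = 0.105 on the log10 scale. A spurious 5% reduction (0.022) is declared a significant benefit about 4% of the time, against 2.5% with no effect. A spurious 30% (0.155) is declared so about 32% of the time.

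**The case against.** The one-minute rule is pre-specified, applies equally to both arms and has a sensible purpose, since brief deviations may be contact noise. If sustained deviation is the intended estimand, bringing an episode below a minute is a real gain and nothing is overstated. That stands, but the outcome statements do not define the burden that way.

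The clinical steps in Figures 1 and 2 apply to a reading that is consistently out of range, with one change at a time and reassessment within 30 minutes. This suggests that many treated episodes run well beyond a minute, where the one-minute distortion is small. This also stands. The large distortions in the table belong to the supplementary ten-minute report or to very short mean lengths.

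A reader might infer that episodes are interrupted only in the intervention arm. The documents do not support that: contact alarms stay active in controls, and alarms and sensor repositioning are recorded in both arms (sections 6.4 and 6.5, Adherence). What differs is the response to range deviations. A reader might also infer that nothing planned could reveal a problem. Yet the SAP reports two cut-offs, and a marked gap between them would hint at dependence on duration. It would not give the effect on total time out of range.

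**Conclusion.** The plan defines one burden and reports another, and it has no analysis that connects them. Relative to total time out of range, proportional shortening or splitting of episodes would make the filtered reduction too large. Under exponential lengths, a true halving is overstated by about 5 points or less at one minute when mean length is 3 minutes or more, and by about 22 points at a 1-minute mean. At ten minutes the overstatement is about 10 to 22 points for means of 20 to 10 minutes, and more for shorter means.

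It is tempting to go further and say that any shortened or split episode is scored as removed, so the reported reduction will be overstated. The documents do not support that. A 20-minute episode cut to 5 minutes still counts as 5 under the one-minute rule. A pure fall in frequency gives no bias, and removal of mainly very short episodes gives understatement. Nor do the documents say that a signal gap ends a run. All magnitudes rest on assumed length distributions and on burden measured as time; the size and direction in this trial are unknown.

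**What to change.** In the SAP, Analysis of the outcomes:

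1. Keep the one-minute result. Beside it, add total time below 65% and above 90% with no minimum duration, as in the protocol's Outcomes table, using the same transformation and GEE model, as a pre-specified sensitivity analysis.
2. State one rule, identical in both arms, for when a run ends, how removed or missing samples within a run are treated, and whether a qualifying run counts in full. The documents support no particular bridging length, so the trial team should choose and record one before unblinding.
3. Present the ten-minute figure alongside the unfiltered one and interpret the two together. Number and length of episodes by arm would show which mechanism is at work.

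The unfiltered result is there to show the influence of the filter in either direction; it need not act as a condition for the main conclusion. The cost is some SAP wording and a small amount of code on stored 1.5-second data, with no new data collection. The drawback is that the unfiltered figure carries more brief contact noise, which is why it accompanies the one-minute result and does not replace it.

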## 2. STUDY SITES

### 2.1 STUDY LOCATION/S

Three tertiary NICUs in Australia, 1 in New Zealand and 1 in the US.

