### 6.2 STUDY TYPE & DESIGN & SCHEDULE

1. This trial will be a single-blinded randomised controlled trial with two parallel groups that are stratified for site and gestational age (<26 weeks and  $\geq 26^{+0} - 28^{+6}$  weeks gestation).

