#### 6.4 RANDOMISATION

Central randomisation can be performed by the investigator or by a delegate or by the medical team member (from NICU). Infants assessed as eligible will be randomised to control group or intervention group using variable block randomisation stratified for gestation age (< 26 weeks and ≥ 26 weeks) and study site using web based secure software (REDCap). Randomisation codes for the study will be generated by biostatistician ([name] has generated the codes). Permuted blocks will maintain group balance, infants will be allocated to two groups in a 1:1 ratio. Multiple births (twins) will be assigned to the same arm of the treatment (either intervention or control). Multiple births (twins) will be randomised to the same group, based on negligible intra-class coefficient (ICC) burden of hypoxia within pairs of twins in SafeBoosC-II study (16) and survey of parents of multiple births (19).

To ensure concealment, the block sizes will not be disclosed. Additionally, allocation concealment will be ensured, as REDCap will not reveal the randomisation until the infant has been recruited into the trial.

REDCap will maintain a list of participants enrolled. Each site PI will access only to their site records. The chief investigators will have access to all sites to oversee enrollment. Participants will be given unique codes to protect their identity on all documentation utilised for recording and analysis purposes. Separate data records will be maintained for re-identifiable and de-identified data.

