## **STUDY SYNOPSIS**

The NIRTURE trial is a phase II single-blinded RCT with two parallel groups with 1:1 allocation stratified for site and gestational age (<26 weeks and  $\geq 26^{+0}$ – $28^{+6}$  weeks' gestation) addressing the following question: In premature babies (< 29 weeks gestation at birth), can dedicated treatment with cerebral oxygenation monitoring compared to usual treatment with blinded cerebral oxygenation monitoring, reduce the burden of cerebral hypoxia and hyperoxia in the first 5 days? The trial will use a neonatal population specific sensor and near infrared spectroscopy device from a single manufacturer.

Study design

[figure not shown]

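### Site is a randomisation stratum but is in no analysis model, and further covariates are picked by significance between arms: a conservative test if site matters, and a covariate set left to chance

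*Combined protocol and SAP*

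**What the plan says.** Protocol section 6.4 uses "variable block randomisation stratified for gestation age (< 26 weeks and ≥ 26 weeks) and study site". Section 6.2 and the SAP synopsis agree ("two parallel groups that are stratified for site and gestational age"; "1:1 allocation stratified for site and gestational age"). Section 2.1 lists the sites: "Three tertiary NICUs in Australia, 1 in New Zealand and 1 in the US", five in all.

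On the model, the SAP section on analysis of the outcomes makes one covariate mandatory: "A fixed adjustment for gestational age category will be included as an a priori specified variable". The stratification variables otherwise appear only here: "Sub-group analysis for stratification variables will be performed". Nothing makes site a covariate, a random effect or a cluster. Protocol section 9.3 names no covariates for the primary GEE; the only dependence it models is between twins.

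On further covariates, the SAP states "Adjusted models will be used to explore predictors of outcomes" and then "Variables that differed significantly between the two groups, and could plausibly contributory to the outcome, will be considered for adjustment". It gives no candidate list, no significance level for the screen, and no restriction to variables measured before randomisation.

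**The concern.** Stratified blocks force the arms to be balanced within sites. If burden differs between sites, the treatment difference then varies less from trial to trial than under simple randomisation. A model that omits site leaves the site differences in the residual variance, so it reports the larger standard error. Confidence intervals are too wide, and power that the design has already secured is not used. Site could well predict burden: section 6.5 (concomitant care) leaves care to each unit's practice, and the units lie in three countries.

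The covariate rule is a separate weakness. Under randomisation, a significant baseline difference is chance and says nothing about whether the variable predicts burden. A strongly prognostic variable that happens to balance is left out, and an irrelevant one that happens not to balance can come in. As worded, the rule also does not shut out variables on the treatment pathway. The algorithms in Figures 1 and 2 act through oxygen, ventilation, circulatory support and transfusion, and such variables are expected to differ between arms if the intervention works.

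**Working it through.** **The plan's own figure.** From the SAP sample size section: difference 0.3 and SD 0.5 on the log scale, two-sided 5%, 80% power. Normal approximation: n = 2(1.96 + 0.842)² × 0.5² / 0.3² = 43.6, so 44 per group. With the t distribution 45 are needed (power 80.4% at 45, 79.5% at 44). Design effect 1 + (1.3 − 1) × 0.1 = 1.03, and 45 × 1.03 = 46.4, so 47 per group. The plan's 47 is reproduced, and nothing below changes it.

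**Effect of omitting site: formula.** Assumptions not in the documents: gestational age explains 10% of variance and site a share s. Take N = 100, SD 0.5 and exact balance within strata.

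- Reported SE without site: √(4 × 0.25 × 0.9 / 100) = 0.0949, whatever s is.
- SE with site: √(4 × 0.25 × (0.9 − s) / 100) = 0.0922, 0.0894, 0.0837 and 0.0775 for s = 5, 10, 20 and 30%.
- Ratio √(0.9 / (0.9 − s)) = 1.03, 1.06, 1.13 and 1.22.
- Actual size of the nominal 5% test, P(|Z| > 1.96 × ratio): about 4.4, 3.8, 2.6 and 1.6%.

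**Effect of omitting site: simulation.** 4,000 trials per scenario, five sites by two gestational strata, permuted blocks of 4 or 6, linear model, gestational age in both models. Further assumptions: 35% of babies under 26 weeks, sites of equal expected size, one baseline variable explaining 20% of variance, no twins. Monte Carlo error is about 0.3 points for type I error and 0.5 for power.

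| Site share of variance | Type I, GA only | Type I, GA + site | Power, GA only | Power, GA + site | Gain (points, unrounded) |
|---|---|---|---|---|---|
| 0% | 4.9% | 4.7% | 87.8% | 87.7% | 0.0 |
| 5% | 4.4% | 5.0% | 87.9% | 88.8% | 1.0 |
| 10% | 3.6% | 4.9% | 89.2% | 91.5% | 2.3 |
| 20% | 2.7% | 4.4% | 90.2% | 94.4% | 4.2 |
| 30% | 2.2% | 5.3% | 91.1% | 96.6% | 5.5 |

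The simulation agrees with the formula. At 30% the formula gives a lower size because it assumes exact balance, which incomplete blocks do not deliver. The power levels assume all 100 babies contribute, so the differences matter more than the levels.

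**Covariate screen.** With k independent baseline candidates, the chance that at least one differs at p < 0.05 is 1 − 0.95^k: 23% for 5, 40% for 10, 64% for 20. In the same simulation with 10 candidates, one of them prognostic, adding whichever were flagged to the gestational age model gave type I error of 4.2, 3.8, 3.2, 2.2 and 1.6% for site shares of 0, 5, 10, 20 and 30%. Power was 87.9, 88.2, 89.0, 90.2 and 91.1%, no gain over gestational age alone. Naming site and the prognostic variable in advance gave 94.1, 95.3, 96.7, 98.5 and 99.6%.

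**Twins and GEE.** With 70 singletons, 15 twin pairs and within-pair correlation 0.1, an uncorrected sandwich variance with a normal reference gave type I error of 5.8, 5.1, 4.4 and 3.4% without site (shares 0, 5, 10 and 20%). With site added it was about 6 to 7%. A small-sample correction brought the latter to about 4.3 to 4.6% and still raised power when site explained 10% or more.

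**The case against.** The strongest reply is that little is at stake. If site explains nothing, the standard error is right; at 5 to 10% of variance it is only 3 to 6% too large. Nothing in the documents supports a share of 20 or 30%. The error is conservative. This stands, and it limits the size of the point.

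A reader might infer from an omitted stratum that standard errors are wrong in a way that produces false positives. The documents do not support that: leaving site out makes the test more conservative, not less. The one inflation found came from the uncorrected sandwich variance. It was largest with site added, so it bears on how the fix is worded.

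A reader might also infer that the primary result will come from a data-driven model. The screening sentence directly follows one on exploring predictors, says only that variables will be considered, and also asks for plausibility; protocol section 9.3 gives the primary GEE without covariates. So the screen may never touch the primary comparison, and applied mechanically to baseline variables it did not inflate type I error. But the gestational age adjustment sits in the same run of sentences, so the text does not settle which model is primary.

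Finally, a reader might infer that the trial will adjust for treatments on the causal pathway. The SAP names none. The rule can be read as referring to baseline characteristics, so this is a gap in wording, not a stated plan.

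It cannot be replied that robust GEE errors repair the omission: without site, the size still fell to 4.4 and 3.4% at site shares of 10 and 20%.

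**Conclusion.** The point holds as a modest gap in specification. Site is a randomisation factor and is absent from every stated model. To the extent that it predicts burden, the test is conservative: about 3.6% actual size and 2 points of power lost if site explains 10% of variance, about 2.2% and 5.5 points at 30%, and nothing at 0%. These shares are assumptions, as are the 10% for gestational age, the block sizes and the mix of strata.

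The significance screen is a poor rule wherever it applies. It does not pick prognostic variables, brings no power, leaves the model open until the data are seen, and does not bar post-randomisation variables. Whether it governs the primary comparison cannot be told from the text. The change is worth making because it costs so little.

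**What to change.** State the primary model in full in the SAP: GEE for log burden on arm, gestational age stratum and site as fixed effects, clustered on twin pair. Specify a small-sample-corrected sandwich variance with a t reference, and a rule, fixed before unblinding, for pooling very small sites. Delete the criterion based on significant differences between arms. If more covariates are wanted, name them before unblinding, from pre-randomisation variables only (for example sex, birth weight, inborn or outborn), and confine them to a secondary model.

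The cost is SAP wording, up to four degrees of freedom for five sites, and about a point of power under the corrected variance if site explains nothing. The sample size stays at 47 per group.
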